## Abstract

**Introduction:**

Research in people with relapsing remitting multiple sclerosis (PwRRMS) is increasingly focusing on non-motor symptoms like cognitive impairment, fatigue and depression. Due to the high negative impact on quality of life and high socioeconomic costs based on these symptoms, more specific research to improve non-motor symptoms is needed. Transcutaneous auricular vagus nerve stimulation (taVNS) has been found to be a cognitive enhancer in preclinical research and was successfully used for the treatment of psychiatric and neurological disorders to combat dysfunctional cognitive and affective processes. However, the capacity of taVNS to improve cognitive and other non-motor symptoms in PwRRMS has not been tested yet. The aim of this study is to evaluate the therapeutic potential of taVNS on cognitive processing speed. Based on ample evidence demonstrating that taVNS promotes adaptive cognitive and affective processes, we hypothesised that taVNS would alleviate cognitive processing speed in PwRRMS.

**Methods and analysis:**

This study protocol describes the prospective, single-centre, SHAM-controlled, single-blinded trial with a planned sample size of 60 participants (30 PwRRMS, with a diagnosis of multiple sclerosis according to McDonald criteria and 30 healthy controls; age: 18–50 years). The Symbol Digit Modalities Test (SDMT) will be used to determine cognitive processing speed, Beck Depression Inventory-II to determine depression and Fatigue Scale for Motor and Cognitive Functions to determine fatigue. The severity of multiple sclerosis will be assessed using the Expanded Disability Status Scale. After baseline assessment, a taVNS protocol (duration: 30 min, tolerance threshold, pulse width: 250 μs, stimulation frequency: 25 Hz, 30 s on/30 s off) will be applied, followed by post-intervention assessment.

**Ethics and dissemination:**

The study was reviewed and approved by the local ethics committee of the University Medical Centre Greifswald (study reference number: BB137/24). Clinical trial registration: www.drks.de, number: DRKS00034912. Study results will be disseminated through academic conferences as well as peer-reviewed publications.

**Trial registration number:**

DRKS00034912.

STRENGTHS AND LIMITATIONS OF THIS STUDYThis is the first study assessing the effect of a non-invasive transcutaneous auricular vagus nerve stimulation intervention on non-motor symptoms in people with multiple sclerosis.Due to the single centre setting and the planned sample size, statistical power to detect possible smaller effect sizes as well as the external validity of this study might be limited.Verum and SHAM interventions are included in this study, and the primary and secondary outcomes are clearly defined.SHAM intervention is performed at the earlobe which is in very rare cases innervated by vagal nerve fibres.Well-established tests and questionnaires are used for the neuropsychological assessment like the Symbol Digit Modalities Test, the Beck Depression Inventory-II and the Fatigue Scale for Motor and Cognitive Functions.

## Introduction

 Relapsing remitting multiple sclerosis (RRMS) is one of the most prevalent neurological disorders, especially in young adults.^1^ The disease can lead to many different neurological signs and symptoms, such as paresis or hypoaesthesia, as well as cognitive impairment occurring in 40%–70% of people with RRMS (PwRRMS).^2^ The most prevalent impaired cognitive domain is processing speed, which has a significant impact on quality of life.^3^ While highly effective immunomodulatory drugs are available to suppress disease activity, there are no specific treatment options for cognitive impairment.

A new therapeutic approach might be transcutaneous auricular vagus nerve stimulation (taVNS), which is a safe, non-invasive method that stimulates the auricular branch of the vagus nerve.^4^,^7^ Stimulation of the auricular branch of the vagus nerve leads to an activation of the nucleus tractus solitarius (NTS), which, in turn, leads to an activation or modulation of different cortical and subcortical brain regions, including the serotoninergic raphe nuclei, the cholinergic nucleus basalis of Meynert, the pedunculopontine nucleus and the noradrenergic locus caeruleus.^8^,^13^ Accordingly, taVNS leads to a widespread modulation of different neurotransmitter systems, including the serotonergic, cholinergic and noradrenergic, but also the GABAergic system.^10 14 15^ The effects of the taVNS on these neurotransmitter systems have been demonstrated in various animal experiments.^16^,^20^ Building on these studies, several assessments were carried out on healthy volunteers, which used functional MRI(fMRI) to demonstrate the modulation of the above-mentioned neurotransmitter systems due to taVNS.^14 21^ The structures modified by taVNS, include, among others, the locus caeruleus and the NTS, but also cortical areas such as the postcentral gyrus, the cerebellum, the prefrontal cortex, the insula and the anterior cingulate.^14 21^ The interplay of these neural circuits has been shown to underlie cognitive and affective processes, such as executive function.^22^

Recent studies provide evidence for taVNS to express beneficial effects on cognitive outcomes in healthy adults, showing improvements, for example, in spatial working memory, executive functions, learning or motivation after taVNS compared with control conditions.^23^,^30^ Furthermore, there are first results showing an improvement in cognition when long-term stimulation (n=76; 2-week taVNS, daily use for 4 hours/day) is used in healthy adults.^31^

Moreover, the effect of taVNS on cognition has also been assessed in neurological conditions, including epilepsy, stroke and mild cognitive impairment due to neurodegenerative disorders.^32^,^34^

Until now, the effect of taVNS on processing speed in PwRRMS has never been assessed. Based on the already existing promising effects on cognitive domains in other diseases due to neurotransmitter changes and the cortical and subcortical alterations due to the neurotransmitter modification, taVNS might have the potential to alter processing speed in PwRRMS.

In 2020, Grothe *et al* revealed the functional representation of the Symbol Digit Modalities Test (SDMT) in PwRRMS. The results showed an activation of frontal, occipital, parietal and cerebellar areas under performance of the SDMT.^35^ The neuroanatomical overlap between cortical areas that are activated due to taVNS and the areas that are crucial for processing speed performance (cerebellum and prefrontal cortex) might support the hypothesis that taVNS can alter processing speed performance.^14 21 35^

Based on the neurotransmitter network alterations and the overlap between the cortical and subcortical areas that are affected by taVNS and are responsible for processing speed performance in PwRRMS, the aim of this study is to assess the effect of taVNS on processing speed in PwRRMS (primary). Furthermore, the association between disease-related variables (disease severity, fatigue and depression) and the change in processing speed will be evaluated (secondary). This protocol is intended to describe the background, planned methods and procedures for the proposed study.

## Methods and analysis

### Study design

This is a prospective, single-centre, single-blinded, SHAM-controlled trial to evaluate the effect of taVNS on non-motor symptoms in PwRRMS. Study begin will be 1 May 2025. The study was reviewed and approved by the local ethics committee of the University Medical Center Greifswald (study reference number: BB137/24). Clinical trial registration: www.drks.de, trial registration number: DRKS00034912.

### Study population and recruitment

In total, 60 subjects will be included in this study, 30 PwRRMS and 30 healthy controls. PwRRMS will be recruited from the MS outpatient clinic of the University Medicine Greifswald. The healthy control group will be recruited through advertisement. Every participant will sign informed consent. An example of the participant consent form is added as online supplemental material.

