### Inclusion/exclusion criteria

#### Inclusion criteria

Participants will be eligible for the study according to the following criteria: (1) age: 18–50 years; (2) able to agree to participate and sign informed consent; and (3) diagnosed with RRMS according to the McDonald criteria 2017 (patient group).^36^

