#### Exclusion criteria

Exclusion criteria are: (1) history or current acute or chronic illness (eg, dermatological diseases because of a potential irritation and worsening due to a stimulation at the earlobe or specific cardiovascular diseases (such as bradycardia, myocardial infarction and heart failure) as taVNS potentially leads to a modulation of heart rate variability which, in turn, might have a negative impact on cardiac pathologies)^37^; (2) presence of other neurological diseases (except for RRMS in the patient group) or psychiatric diseases; (3) history of medication (except immunomodulatory medication in RRMS as well as symptomatic treatment, including antispastic medication); (4) pregnancy; and (5) participation in other, possibly conflicting studies.

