#### Baseline assessment

At the beginning, a medical interview will be conducted in which the relevant epidemiological and demographical data, including age and sex, are collected. Following the interview, a neuropsychological examination will be carried out, consisting of SDMT, BDI-II, FSMC and EDSS (the latter only used in PwRRMS).

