#### Secondary

Exploratory outcome measurements will be:

The processing speed in healthy controls in relation to the stimulation method (SHAM stimulation and verum stimulation), operationalised by the SDMT accuracy.The difference in the change in processing speed (SHAM stimulation vs verum stimulation) between the groups (PwRRMS/controls).The association between disease-related variables (disease severity, fatigue and depression) and the change in processing speed.

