#### Data analysis

Statistical analysis will be conducted using SPSS Statistics V.25 (IBM SPSS Statistics for Mac, V.25.0. Armonk, NY: IBM Corp). With a total number of n=30 in each study arm, a normal distribution can be assumed. Based on this, normally distributed variables will be presented as mean±SD. Non-normally distributed variables will be presented as median and (IQR). A linear mixed model will be performed for the primary/secondary outcomes using ‘time’ (pre vs during), ‘stimulation’ (taVNS vs sham), ‘group’ (MS vs controls), ‘session order’ (Session 1 vs Session 2) and ‘control variables’ (age, fatigue, depression and severity) as fixed, ‘participant’ as random effects. A significance level of 5% will be used to test the hypotheses.

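### Controls come by advertisement with no age or sex balancing described, so the exploratory PwRRMS-versus-control difference in the taVNS response is open to confounding that a main-effect age term cannot remove

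*Protocol article*

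**What the plan says.** Under Study population and recruitment, the protocol article sets the numbers ("In total, 60 subjects will be included in this study, 30 PwRRMS and 30 healthy controls") and names two different sources: "PwRRMS will be recruited from the MS outpatient clinic of the University Medicine Greifswald", and "The healthy control group will be recruited through advertisement".

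The Inclusion criteria that apply to both groups are "1) age: 18–50 years; (2) able to agree to participate and sign informed consent". The exclusions are also shared, with exceptions for patients, for example "presence of other neurological diseases (except for RRMS in the patient group) or psychiatric diseases". No criterion concerns sex, and no matching or banding appears under recruitment, eligibility or Study schedule.

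Under Baseline assessment, "relevant epidemiological and demographical data, including age and sex, are collected". Under Data analysis, the control variables of the linear mixed model are "age, fatigue, depression and severity". Sex is not among them.

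The outcome at issue is listed under Secondary, where the outcomes are labelled exploratory: "The difference in the change in processing speed (SHAM stimulation vs verum stimulation) between the groups (PwRRMS/controls"). The primary outcome is SHAM versus verum within PwRRMS. Randomisation concerns only which stimulation comes first.

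**The concern.** The cross-over makes each participant their own control, which protects the verum-versus-SHAM comparison inside each group. It does not make the two groups comparable with each other, because belonging to a group is observed and not allocated. If clinic patients and advertisement respondents differ in age or sex, and the acute response to taVNS depends on age or sex, a group difference in response may reflect who was recruited and not MS. A real difference could be masked in the same way.

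A reader who sees age among the control variables may think that this is already handled. As a main effect it is not, for the reason shown in the working. At stake is the interpretation of one exploratory outcome, one of the two listed outcomes that plainly use the 30 controls.

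**Working it through.** The documents contain no figure for this point: no expected age or sex distribution, no SDMT standard deviation and no effect size. Nothing can be reproduced, so the check is algebra plus an illustration on stated assumptions.

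**1. What cancels.** For each participant, take

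D = (verum during − verum pre) − (SHAM during − SHAM pre).

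Anything that shifts all four scores equally drops out, including the effect of age or sex on SDMT level. A within-session practice gain that is the same under both stimulations also drops out, even if it depends on age. With complete data, a main effect of age or sex in the model therefore cannot alter the group comparison of D.

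**2. What remains.** Let the expected D be τ + δ·(PwRRMS) + γ_age·age + γ_sex·(female). The difference between groups is then

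δ + γ_age × (difference in mean age) + γ_sex × (difference in proportion female).

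The last two terms are the bias. Each is a product, so it is zero if the imbalance is zero or if the modification is zero.

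**3. Size on assumed inputs (SDMT points).**

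| Age gap | Sex gap | No modification | Age 0.1/year | Sex 2 points | Both |
|---|---|---|---|---|---|
| 0 years | 0 | 0 | 0 | 0 | 0 |
| 5 years | 0.20 | 0 | 0.5 | 0.4 | 0.9 |
| 10 years | 0.20 | 0 | 1.0 | 0.4 | 1.4 |
| 10 years | 0.30 | 0 | 1.0 | 0.6 | 1.6 |

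For example, 0.1 × 10 + 2 × 0.30 = 1.6. A slope of 0.2 points per year would give 0.2 × 10 = 2.0 from age alone. That slope implies a 32 × 0.2 = 6.4-point swing in acute response across ages 18–50, which is a strong assumption.

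**4. Simulation.** 150 trials per scenario were simulated with 30 per group, nominal mean ages 38 and 28 (SD 6, limited to 18–50), 70% and 50% female, participant SD 8, residual SD 3 and a true group effect of zero. All of these are assumptions. Entries are the mean estimated group difference, with the Monte Carlo standard error in brackets.

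| Modification | No covariates | Age main effect | Age and sex main effects | Age and sex × stimulation × time |
|---|---|---|---|---|
| None | −0.02 (0.13) | −0.02 (0.13) | −0.02 (0.13) | 0.00 (0.18) |
| Age 0.1/year | 1.02 (0.12) | 1.02 (0.12) | 1.02 (0.12) | −0.15 (0.16) |
| Sex 2 points | 0.31 (0.11) | 0.31 (0.11) | 0.31 (0.11) | −0.07 (0.16) |
| Both | 1.49 (0.12) | 1.49 (0.12) | 1.49 (0.12) | 0.16 (0.17) |

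Main effects leave the estimate unchanged. The interaction terms bring it to zero within simulation error. The ratio of standard errors (0.16/0.12 = 1.33 up to 0.16/0.11 = 1.45, from rounded values) puts the cost at a standard error roughly a third to nearly a half larger under this 10-year gap.

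**5. Scale.** With residual SD 3, D has SD √(4 × 9) = 6, and the group difference has standard error √(2 × 36/30) = 1.55. A bias of 1.4 points is then 1.4/1.55 = 0.9 standard errors. By the normal approximation at two-sided 5% (the article does not state sidedness), power with 30 per group is Φ(d√15 − 1.96): 49% at d = 0.5 and about 80% at d = 0.72. The comparison has little precision to spare for adjustment afterwards.

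**The case against.** The strongest reply has four parts.

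- **The article is condensed.** Matching could be specified in a fuller protocol. Data analysis writes out no interactions at all, not even the group by stimulation by time term that this outcome needs, so the list is not a full model specification and age need not be a main effect only. This stands as a limit: the point about the age term is conditional on how it is entered. The recruitment route, the eligibility criteria and the covariate names are printed, however, and none of them provides balance on age or sex.
- **Shared criteria.** A reader might infer that the age limit is all the groups have in common. The documents do not support that: the consent criterion and the exclusions apply to both. It is true only of demographic criteria.
- **No demonstrated bias.** A reader might infer that the comparison is confounded as a matter of fact. That needs both an imbalance and effect modification, and the documents establish neither. With no modification, the simulated bias was −0.02 (0.13) despite a 10-year age gap and a 20-point sex gap. Differential practice is not a separate route, because stable practice cancels between the two sessions.
- **Limited stake.** The outcome is labelled exploratory, and the article already concedes limited sample size and power. This stands and lowers the priority, although the limitations it lists do not mention comparability of the controls.

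**Conclusion.** The point holds in a limited form. As printed, the plan leaves the exploratory group difference in the verum-minus-SHAM change open to confounding by age and sex, and neither the listed age term as a main effect nor an added sex main effect would close that gap. The primary comparison within PwRRMS and the verum–SHAM comparison within controls are unaffected.

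The size is unknown. On the tabulated assumptions it runs from 0 to 1.6 SDMT points, and zero is a genuine possibility.

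It would also go too far to infer that matching is the only workable control. In the simulation, covariate by stimulation by time terms removed the bias at 30 per group, at a cost in precision. They would fail only if the age distributions barely overlapped, and nothing in the documents suggests that. Matching is preferable because it is cheap and keeps the precision. This is a worthwhile design improvement for one secondary outcome, not an error that endangers the trial's main result.

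**What to change.** - **Recruitment.** Frequency-match controls to the PwRRMS by sex and age band (for example 18–29, 30–39 and 40–50), choosing among advertisement respondents as the patient group fills. The planned start was 1 May 2025; if enrolment has begun, balance the remaining controls.
- **Analysis.** As a sensitivity analysis of the group difference, add age × stimulation × time and sex × stimulation × time terms. Adding sex only as a main effect would leave this contrast where it was.
- **Reporting.** Interpret the group difference cautiously if imbalance remains.

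Cost: no extra participants or procedures. Some respondents are declined or wait for a free cell, so control recruitment is slightly slower. The sensitivity model loses some precision.

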#### Patient and public Involvement

Patients as well as the public were not involved in the study design, conduct, reporting or dissemination plans of this research.

### Inclusion/exclusion criteria

#### Inclusion criteria

Participants will be eligible for the study according to the following criteria: (1) age: 18–50 years; (2) able to agree to participate and sign informed consent; and (3) diagnosed with RRMS according to the McDonald criteria 2017 (patient group).^36^

#### Exclusion criteria

Exclusion criteria are: (1) history or current acute or chronic illness (eg, dermatological diseases because of a potential irritation and worsening due to a stimulation at the earlobe or specific cardiovascular diseases (such as bradycardia, myocardial infarction and heart failure) as taVNS potentially leads to a modulation of heart rate variability which, in turn, might have a negative impact on cardiac pathologies)^37^; (2) presence of other neurological diseases (except for RRMS in the patient group) or psychiatric diseases; (3) history of medication (except immunomodulatory medication in RRMS as well as symptomatic treatment, including antispastic medication); (4) pregnancy; and (5) participation in other, possibly conflicting studies.

### Interventions

#### Neuropsychological evaluation

##### Symbol Digit Modalities Test

Cognitive processing speed will be assessed using the SDMT.^38^,^40^ The SDMT comprises two parts: a legend with the numbers 1 through 9 with corresponding, meaningless symbols for each number (in total nine different symbols) as well as several lines with symbols in a random order and a space under each symbol. The subjects have to complete as many lines in 90 s as possible (telling the correct number under the corresponding symbol according to the legend at the top of the page). For the planned study, the total score, which is defined as the total amount of correct matched symbol–number pairs, will be taken into account for analysis.^41^ Different SDMT versions will be used to control multiple testing and to avoid learning effects.

##### Beck Depression Inventory-II Test

Depression will be quantified with the Beck Depression Inventory-II Test (BDI-II; Hogrefe Austria GmbH, Wien, Austria).^42^,^45^ The test consists of 21 groups of statements with corresponding points scaling from 0 to 3 towards a specific topic. The participants can choose only one statement for each topic. The total score (sum of the point values of all chosen statements) indicates the presence of depression as well as a graduation between mild, moderate and severe depression.^43 44^

##### Fatigue Scale for Motor and Cognitive Functions

The Fatigue Scale for Motor and Cognitive Functions (FSMC) is a screening tool with a high sensitivity as well as a high specificity to detect trait fatigue and furthermore differentiates between motor and cognitive fatigue.^46^ The FSMC consists of 20 items with 1–5 points for each item (1=‘does not apply at all’ to 5=‘fully applies’; 1–5 points).^46^ The total score as well as the sub-scores for cognitive and motor fatigue will be analysed in the planned study.

##### Expanded Disability Status Scale

The Expanded Disability Status Scale (EDSS) will be performed to evaluate the degree of disability in PwRRMS. The scale ranges from 0 to 10 and is primarily focused on motor skills.^47^ A score of 0 describes normal clinical findings whereas a score of 10 means death due to multiple sclerosis.^47 48^

### taVNS administration

Either SHAM stimulation or verum stimulation will be performed via a taVNS-R device (taVNS Technologies GmbH, Erlangen, Germany). This device consists of two iridium-covered, round titanium electrodes of 2 mm diameter, applying a small electric current to the skin. The device will be attached to the left ear. For verum stimulation, the electrodes will be applied to the cymba conchae; for SHAM stimulation, the electrodes will be applied to the left-sided earlobe of the subject. Before the stimulation, the ear of the subject will be prepared using an alcohol wipe for cleaning the skin from, for example, particles. Once attached to the ear of the subject, the stimulation intensity will be individually calibrated to ensure that intensity will be at tolerance threshold (defined as a painless but strong tingling sensation). For this, the applied current will be increased stepwise (100 μA steps) until a painful sensation is reported by the subject. The stimulation current will be noted and the current will be reduced until the subjects feel a strong tingling sensation without pain perception (this current will also be noted). This procedure will be repeated twice and the perception threshold will be calculated as the mean value of the four tested current values.^29^

The stimulation will be delivered continuously 15 min before, during, as well as 5 min after the neuropsychological testing (SDMT) regardless of SHAM stimulation or verum stimulation. The following stimulation parameters will be applied: pulse width: 250 μs, stimulation frequency: 25 Hz, 30 s on/30 s off, motion threshold: off, ramp-up: off, buzzer: off. Stimulation settings will be controlled by a taVNS Research App (taVNS Technologies) via bluetooth connection with a mobile phone. In order to control for circadian influences within subjects, stimulation will be applied at a constant time for each participant (when the participant will be assessed in the morning, the second assessment will also be performed in the morning).

